#### Blinding

Patients, clinical raters and data analysts are blind to treatment conditions. As the treatment group is easily realized by the number of brain areas stimulated (one in the control group vs. three in the treatment group), patients are informed that two active stimulation procedures are compared without specifying the exact difference between the two protocols.

#### Randomization

An online generator was used to prepare a balanced randomization list before the trial started. The whole sample was used as one block. Only the nonblinded clinical staff are granted access to this list and perform randomization prior to the first treatment session.

#### Determination of sample size

The study is designed to find an interaction effect between group (single-site vs. multisite) and time (baseline, end of treatment). Based on our pilot data
[21] a small effect size of *f* = 0.1 for this interaction effect is assumed. Although small, such an effect is still an important step in tinnitus management. If the study sample size is determined to provide sufficient power (0.8) for detection of such an effect in a repeated-measures analysis of variance (with α = 0.05), a total of 42 tinnitus patients have to be examined. Due to the complex and time-consuming study design, a higher patient dropout rate than usual is assumed. A total of 50 patients (25 per group) are therefore planned to be included in the study.

#### Statistical analysis

Missing data entries are handled with the last observation carried forward method. For the comparison of treatment responders in both groups, a chi-square statistic is calculated. For all secondary outcomes, an analysis of variance is used with the between-subjects factor group (multisite rTMS vs. single-site rTMS) and the repeated-measures factor time (baseline vs. end of treatment vs. all follow-up time points). EEG and (functional) MRI data are analyzed with MatLab-based analytic software (MathWorks, Natick, MA, USA; EEGLAB; FieldTrip; SPM). For both EEG and functional MRI data, different exploratory analyses focusing predominantly on connectivity measures will be done. As it is hypothesized to find altered connectivity patterns in tinnitus patients, imaging/EEG data of both patient groups are compared with data for the control group (baseline measurements of the tinnitus groups vs. single measurement of the controls). Furthermore, longitudinal analyses will be performed to test for a change of the connectivity patterns from before to after rTMS treatment (contrast: pre rTMS vs. post rTMS). Correlations of imaging data and questionnaire scores are used to identify potential predictors for rTMS outcome. As the present protocol has a clinical focus, we do not go into detail concerning the EEG and functional MRI analyses at this point.

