### Objectives

Based on the findings in the pilot study, we hypothesize that the reduction of the Tinnitus Questionnaire (TQ) score as well as the number of treatment responders after 10 days of rTMS treatment and after follow-up periods of 3 and 6 months are higher when patients are treated using the new multisite stimulation protocol in comparison with single-site stimulation of the temporoparietal cortex. Treatment response is defined as an improvement of ≥5 points in the TQ score
[22]. Further aims of the study are as follows: to compare multisite stimulation with single-site stimulation with respect to a change of tinnitus severity as measured by the TQ, the Tinnitus Handicap Inventory (THI) and numeric rating scales assessing the loudness and annoyance of the tinnitus percept (baseline vs. end of treatment and all follow-up visits); to compare single-site stimulation with multisite stimulation with respect to a change in secondary outcomes such as quality of life, hyperacusis and depressive symptoms (baseline vs. end of treatment and all follow-up visits); to replicate and expand findings concerning the neural correlates of tinnitus using resting state EEG, MRI and resting-state functional MRI; to examine whether successful treatment with rTMS is correlated with changes in brain structure and activity; to examine whether treatment with multisite rTMS induces different brain changes than treatment with single-site rTMS (we assume that network alterations associated with tinnitus can be influenced more effectively using multisite stimulation as compared with single-site rTMS); and to determine whether brain structure and activity as measured by EEG and functional MRI at baseline are predictive for treatment response.

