#### Outcome measures

The primary outcome measures are the change in the TQ score from baseline to end of treatment (interaction effect time × group) as well as the number of treatment responders as defined by a reduction in the tinnitus questionnaire score of ≥5 points at the end of treatment. Secondary outcome measures are changes in all scales and questionnaires (TQ, THI, numeric rating scales, Major Depression Inventory, World Health Organization Quality of Life assessment, hyperacusis questionnaire) between baseline and end of treatment as well as between baseline and all follow-up periods. Furthermore, the number of treatment responders at all follow-up time points is examined.

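### Last observation carried forward as the only missing-data method can bias the primary comparison in a direction set by the dropout pattern, assumes the persistence claimed at 3 and 6 months, and partly erodes the dropout allowance

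*Protocol article*

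**What the plan says.** The Statistical analysis section gives one rule for missing data: "Missing data entries are handled with the last observation carried forward method". It does not restrict the rule to particular outcomes or visits, and it names no alternative or sensitivity analysis.

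Both primary outcomes sit at end of treatment (Outcome measures). One is the group difference in TQ change from baseline. The other is the number of responders, defined by a "reduction in the tinnitus questionnaire score of ≥5 points at the end of treatment".

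Follow-up is part of the hypothesis. The Objectives section expects TQ reduction and responder numbers that "after 10 days of rTMS treatment and after follow-up periods of 3 and 6 months are higher" under multisite stimulation. The follow-up results are secondary outcomes and enter a group by time analysis of variance over all visits.

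The Determination of sample size section arrives at 42 patients for 80% power and then enrols 50, because "a higher patient dropout rate than usual is assumed". It states no dropout rate, no timing and no split by arm.

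**The concern.** The plan expects a notable amount of missing data and commits to filling all of it with single copied values, which are then analysed as if observed. What the copy means depends on when the patient leaves.

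- **Lost before end of treatment.** The copied value is the baseline score, unless a TQ is taken during treatment. The patient then counts as zero change and as a non-responder in both primary analyses.
- **Lost after end of treatment.** The end-of-treatment score is copied to months 3 and 6. Any fading of benefit in these patients is ruled out by construction, although durability is one of the things the trial sets out to show.

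At stake are the size, and under unequal dropout the direction, of the error in the primary contrast; the credibility of the follow-up claims; and part of the power that the eight extra patients were meant to secure.

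**Working it through.** **Inputs from the article.** Effect size f = 0.1, alpha 0.05, power 0.80, two groups, two time points, 42 evaluable patients, 50 enrolled (25 per arm).

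**Assumptions, not in the article.** Baseline to end-of-treatment correlation rho = 0.9; TQ SD 17; the dropout patterns below; the mean improvement in the single-site arm, varied from 0 to 7.6 points (one SD of change). The SD only converts results to points. The shrinkage factors for balanced loss depend on neither SD nor rho.

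**1. Reproducing the 42.** For the group by time interaction, lambda = f² × N × m / (1 − rho). With N = 42 and m = 2, lambda = 0.01 × 42 × 2 / 0.1 = 8.4. On 1 and 40 degrees of freedom, power is 0.807. So 42 is reproduced at rho = 0.9. With all 50 observed, lambda = 10 and power is 0.873. The implied loss is 1 − 42/50 = 16%.

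**2. In points.** SD of change = 17 × √(2 × 0.1) = 7.6. The difference in change is 4 × 0.1 × 17 = 6.8 points, or 0.894 SDs of change.

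**3. Expected primary difference with baseline carried forward.** Let dM and dS be the dropout fractions, and μM and μS the mean improvements, in the multisite and single-site arms. The expected estimate is (1 − dM)μM − (1 − dS)μS.

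- Equal loss d gives (1 − d) times the true difference: 0.84 × 6.8 = 5.7 points at 16%, and 0.92 × 6.8 = 6.3 points at 8%.
- Loss of 24% single-site and 8% multisite, with μS = 7.6 and μM = 14.4: 0.92 × 14.4 − 0.76 × 7.6 = 7.5 points, 1.10 of the true value. With μS = 0 it is 0.92 of the true value.
- Loss of 8% single-site and 24% multisite, same means: 0.76 × 14.4 − 0.92 × 7.6 = 4.0 points, 0.58 of the true value. With μS = 0 it is 0.76.

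**4. Power, by simulation** (25 per arm, missing changes set to 0, two-sample t-test, which for two time points is the interaction test):

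| Loss before end of treatment, both arms | Power over single-site improvement 0 to 7.6 points | Completers only |
|---|---|---|
| 16% | 0.79 falling to 0.68 | 0.81 |
| 8% | 0.84 falling to 0.78 | 0.84 |

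The loss is small when the single-site arm barely improves, because zeros near the mean also reduce the SD. With 42 rather than 50 enrolled and 16% carried forward, power is about 0.60 to 0.72.

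**5. Rejection rate with no true difference.**

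| Loss in the two arms | Both improve 4 points | 8 points | 10 points |
|---|---|---|---|
| 16% and 16% | 5% | 5% | 5% |
| 12% and 20% | 5.3% | 6.1% | 6.6% |
| 8% and 24% | 6.3% | 9.4% | 11.2% |

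At 8% and 24% the bias is 0.16 times the common improvement: 0.6, 1.3 and 1.6 points.

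**6. Responders.** Assume true rates of 30% and 70%. Counting 16% as non-responders turns these into 25.2% and 58.8%. Power is 0.68, against 0.76 for 21 completers per arm and 0.83 with no dropout.

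**7. Follow-up.** If the 6.8-point difference at end of treatment has gone by month 6 and a fraction d per arm left in between, the copied scores produce an apparent difference of d × 6.8: 1.1 points at 16%, 0.5 points at 8%.

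**The case against.** Several stronger readings are tempting and are not supported.

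- **That carrying forward shrinks the primary effect.** This needs similar dropout in both arms. With more loss in the single-site arm, the multisite advantage can be overstated.
- **That it makes the primary test invalid.** Under balanced random loss and no true difference, the end-of-treatment test keeps its 5% level. Inflation needs unequal dropout, and nothing in the article says that one arm will lose more. At 12% and 20% the inflation is slight.
- **That it undoes the dropout allowance.** It does not. At 16% loss, enrolling 50 instead of 42 still gains about 7 to 8 percentage points of power under carrying forward.
- **That 16% will be missing at the primary visit.** The article gives no rate and no timing. It blames a demanding study design, and that design runs to 24 weeks, whereas the primary visit follows a two-week course. The same 16% cannot be placed wholly before and wholly after end of treatment.
- **That every early dropout counts as exactly zero change.** The visit schedule figure is not available here, so a TQ during treatment cannot be ruled out. Stopping treatment also need not mean a missing questionnaire.
- **That a false-positive rate can be quoted for 6 months.** That would belong to a separate 6-month t-test. The planned analysis is an omnibus group by time interaction, and rejecting it is no error if a difference truly existed at end of treatment. Only the bias in the 6-month difference is used here.

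These points limit the size and direction of the effect. They leave standing that one single-imputation rule is fixed for all missing data in a trial that expects much of it.

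**Conclusion.** The concern holds in a limited form. The rule can bias both primary comparisons: towards zero if dropout is balanced, either way if it differs by arm. At follow-up it builds in the persistence that the hypothesis asserts. It erodes, without cancelling, the protection bought by enrolling 50.

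The direction of the argument is secure, because it follows from how the method works. The magnitudes are illustrations. They rest on rho = 0.9 (needed to reproduce 42 but not stated), an SD of 17 for figures in points, and assumed dropout patterns. The power figures at 16% are an upper case for harm under balanced loss, with everyone lost before end of treatment. At half that loss the cost is between almost nothing and about six percentage points.

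The change should be made, though nothing here shows that the trial would fail without it.

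**What to change.** Replace the rule in the Statistical analysis section as follows.

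- Analyse all observed TQ scores of every randomised patient with a likelihood-based mixed model for repeated measures containing group, visit, group by visit and baseline TQ, with no imputation of the continuous score.
- Take the group contrast at end of treatment as primary and the contrasts at 3 and 6 months as secondary.
- Derive responder status by multiple imputation under a compatible model, so that a missing score is not automatically a non-response.
- Keep last observation carried forward as a sensitivity analysis only.

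The cost is analysis wording and minor programming, with no new data and no more patients. The main analysis would rest on data being missing at random given the observed scores, which cannot be verified from the data and should be stated.

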#### Ethical aspects

The study protocol has been approved by the ethics committee of the University of Regensburg (10-101-0169). The study is performed in agreement with the principles of the Declaration of Helsinki. All patients are informed about the purpose and the risks of the study and about their right to withdraw their consent at any time. Patients are only included in the study if written informed consent is given.

## Discussion

rTMS has been used as a treatment approach for chronic tinnitus for several years. Results from clinical trials are heterogeneous; in summary, the effect size of rTMS treatment over the auditory cortex has been shown to be rather small. The idea of interfering with altered brain activity via noninvasive brain stimulation is plausible, however, and the efficacy of a specific treatment protocol depends on the quality of the neurobiological model underlying that protocol. During the last few years, knowledge about the neurobiological mechanisms of tinnitus has advanced
[20]. Neuroscientists have moved away from a model restricted to the auditory system towards the concept of a more widespread tinnitus network. This new model of tinnitus can and should now be used to improve rTMS treatment. The attempt to adapt rTMS treatment to the network model brings several methodological difficulties about which had to be dealt with in the design of this trial. The tinnitus network as described by Schlee and colleagues involves several brain regions, all of which can be stimulated with different frequencies in a different order and with a varying number of stimuli
[17]. One of the many possible treatment protocols therefore had to be chosen
[21]. The attempt of this study is not to find the best of all possible protocols but to determine whether a multisite stimulation protocol based on recent studies on the tinnitus network is superior to the standard protocol used in tinnitus treatment. This reason is also why the standard protocol was used as control treatment instead of a placebo control. Having these constraints in mind, the study is capable of providing useful information about a new way to use rTMS in tinnitus patients. By using EEG and (functional) MRI we are able to determine whether both treatment protocols induce different changes in brain structure and function and whether multisite stimulation serves the purpose of interfering with the tinnitus network. Furthermore, the comparison between clinical changes and changes in neuroimaging findings over time provides a unique opportunity for further specifying the exact role of the neuronal network changes underlying tinnitus perception and distress.

## Trial status

The trial started recruitment in July 2012 and will presumably complete follow-up assessments in 2014.

## Abbreviations

EEG: Electroencephalography; MRI: Magnetic resonance imaging; rTMS: Repetitive transcranial magnetic stimulation; THI: Tinnitus Handicap Inventory; TQ: Tinnitus Questionnaire.
